## Abstract

**Background:**

International recommendations suggest exercise and self-management programs, including non-pharmacological treatments, for knee osteoarthritis (KOA) because they can benefit pain relief and improve function and exercise adherence. The implementation of a combined self-management and exercise program termed PLE^2^NO may be a good method for controlling KOA symptoms because it encourages the development of self-efficacy to manage the pathology. This study will assess the effects of a self-management and exercise program in comparison to an educational intervention (control program) on symptoms, physical fitness, health-related quality of life, self-management behaviors, self-efficacy, physical activity level and coping strategies.

**Methods/Design:**

This PLE^2^NO study is a single-blinded, randomized controlled trial of elderly (aged above 60 yrs old) patients with clinical and radiographic KOA. The patients will be allocated into either an educational group (control) or a self-management and exercise group (experimental). All participants will receive a supplement of chondroitin and glucosamine sulfates. This paper describes the protocol that will be used in the PLE^2^NO program.

**Discussion:**

This program has several strengths. First, it involves a combination of self-management and exercise approaches, is available in close proximity to the patients and occurs over a short period of time. The latter two characteristics are crucial for maintaining participant adherence. Exercise components will be implemented using low-cost resources that permit their widespread application. Moreover, the program will provide guidance regarding the effectiveness of using a self-management and exercise program to control KOA symptoms and improve self-efficacy and health-related quality of life.

**Trial registration:**

NCT02562833 (09/23/2015)

## Background

Osteoarthritis (OA) is the most common type of rheumatic disease [1]. OA is prevalent in elderly populations and has a substantial influence on the health care industry [2, 3]. In the USA, 27 million people, including 12.1 % of the population aged 25–74 years old, are clinically defined as having OA [4].

OA is an active disease [5] that affects all articular tissues [6]. OA can be characterized by examining a person’s symptoms, especially pain [7], which influence the performance of daily living activities [8] and psychological parameters [3]. Among older adults, OA primarily affects weight bearing joints, such as the knee and hip, and is therefore a cause of lower extremity disability [9]. In Portugal, knee OA (KOA) is considered to be the third most prevalent rheumatic disease (affecting 12.4 % of the population) [10].

Most types of interventions that are aimed at managing KOA involve community and primary care [5]. Hence, it is imperative to consider international recommendations that can assist individuals and that are feasible alternatives to health services. The Osteoarthritis Research Society International (OARSI) [11], the American College of Rheumatology (ACR) [12] and the European League Against Rheumatism (EULAR) [13] strongly recommend exercise (including land-based, such as strengthening and aerobic activity or water-based activities) and self-management programs as non-pharmacological treatments for KOA patients.

### Self-management programs

Patient education, information and self-management support are critical for patient cooperation during treatment. Besides OARSI international recommendations (11), several evidence-based studies of self-management programs have demonstrated that it is effective to empower patients to better manage their own chronic diseases [14–26].

Psychoeducational interventions are growing in popularity in the primary care field [24]. Among these efforts, self-management programs deserve special attention. The following three models of chronic disease self-management programs are the most widely used: the Expert Patient Programme [27], the Flinders Model [28], and the Stanford Model [29]. The Expert Patient Programme focuses on increasing patient knowledge to manage conditions, the Flinders Model emphasizes the role that physicians play in building patient self-efficacy, and the Stanford Model uses peer educators to build self-efficacy [30].

Two programs have followed the format of the Stanford Model. These include the Arthritis Self-Management Program (ASMP) and the Chronic Disease Self-Management Program (CDSMP) [31, 32]. The first of these, the ASMP, is a specific program for people with arthritis that was developed in the 1970s at the Stanford Patient Education Research Center [19]. Later, the same group developed a more generic proposal for patients with any chronic condition, the CDSMP. This program has now spread in popularity throughout the US [31, 32] and other countries [17, 18, 23, 25, 33].

A meta-analysis of the ASMP and the CDSMP [34] revealed that improvements were observed in several outcome measures in patients with chronic diseases at 4 and 12-month follow-ups.

### Exercise programs

Studies have demonstrated that exercise benefits patients with KOA [35–46]. The two most recognized approaches for KOA treatment with exercise are land-based [47–49] and aquatic programs [44, 50–53]. A recent systematic review and meta-analysis [54] provided evidence showing that land-based exercise is beneficial for people with KOA because it reduced joint pain and improved physical function and quality of life over the short-term and for at least two to six months after the cessation of treatment. Regarding the exercise mode, studies have demonstrated that there is no difference between the efficacies of strengthening, flexibility plus strengthening, flexibility plus strengthening plus aerobic exercise, aquatic strengthening, aquatic strengthening plus flexibility and a combined intervention that included strengthening, flexibility, and aerobic exercise when each was compared to a no exercise control, and there were no differences between the effect of the interventions on improving functional limitations in people with lower limb OA [55]. Additionally, no difference was observed in the effectiveness of providing pain relief between strengthening and aerobic exercises across eight studies that involved KOA patients [56].

Thus, combining aerobic and muscle strengthening exercises into a single program may produce even better outcomes in arthritis patients [57] than programs based on only one of these components. A program that combined aerobic and resistance exercises significantly improved physical function and daily living activities and reduced pain in older adults with arthritis [40], as well as decreased depression [36, 49, 58, 59]. Another program combined a variety of exercises focused on core strength and balance, flexibility, upper and lower body strength and aerobic conditioning and resulted in improvements in mobility, aerobic endurance, strength, flexibility, and self-reported pain perception [35].

### Nutritional supplements: glucosamine and chondroitin sulfate

Although important, controlling symptoms is not the only target when treating OA patients. Indeed, an ideal treatment for OA should preserve joint structures, improve quality of life and for drug therapy or supplementation, have a good safety profile [60]. It is paramount that the administrator account for side effects that can result from the chronic use of OA pharmacological therapies, such as nonsteroidal anti-inflammatory drugs (NSAIDs) [61]. Therefore, glycosaminoglycans such as chondroitin sulfate (CS) and glucosamine sulfate (GlcN-S) are two natural supplements that are considered to be symptomatic slow-acting drugs for osteoarthritis (SYSADOA) [60].

GlcN-S has been shown to exhibit structure-modifying effects, including small to moderate protective effects on minimum joint spaces after 3 years, in KOA patients [62]. This finding was in agreement with the results of a previous trial that indicated that GlcN-S prevents total knee replacement (TKR) [63].

CS has also been evaluated in different clinical trials that have sought to document both its symptomatic potential and its structure-modifying effects. A recent study [64] demonstrated the efficacy of CS for treating symptoms (i.e., pain and lower-limb function) and concluded that CS is an efficient and safe intervention. Interestingly, CS produced a significant reduction in joint swelling and effusion in a gait study [65].

A double-randomized placebo-controlled clinical trial with a 2-year follow-up of 605 patients with KOA demonstrated that after adjusting for factors associated with structural disease progression, a dietary supplement that consisted of a combination of GlcN-S and CS resulted in significantly less joint space narrowing than was observed with the placebo, whereas neither CS nor GlcN-S alone was effective [66]. A combination of GlcN-S-hyaluronic acid (500 mg) and CS (400 mg) was found to be efficient at providing pain relief and functional improvement in OA patients with moderate to severe knee pain [65]. These findings suggested that a combination of GlcN-S and CS may be more efficient than either CS or GlcN-S alone.

Although some interventions have combined patient self-management with an exercise component, we were unable to identify any study that combined these components with GlcN-S and CS supplementation.

### Aim and hypothesis

The aim of this study is to design and implement a PLE^2^NO program (in Portuguese: Free Program of Education and Exercise for Osteoarthritis) for elderly patients with KOA for a duration of three months. The PLE^2^NO is based on applying the principle of self-efficacy to manage the pathology. When patients gain confidence in taking control of their disease, they are more comfortable exercising and managing OA symptoms and consequently make better decisions about treatment. This allows them to increase their quality of life. To encourage participant’s adherence to and maintenance of the program and to contribute to pain control, all participants will receive a supplement containing CS and GlcN-S.

The following three hypotheses were therefore formulated. H1, self-reported KOA symptoms (i.e., pain and stiffness) and physical fitness will improve more in the self-management and exercise group than in the control group; H2, self-management skills and self-efficacy will improve more in the self-management and exercise group than in the control group; and H3, health-related quality of life, physical activity levels and coping strategies will improve more in the self-management and exercise group.

## Methods and design

### Study design

The PLE^2^NO is a single-blinded, randomized controlled trial with a three-month duration and a six-month follow-up. The participants will be individually randomly assigned to one of two groups: (1) a self-management and exercise group or (2) an educational control group. Both groups will receive supplementation (CS and GlcN-S). Figure 1 provides a flowchart of the PLE^2^NO design. It will not be possible to blind the participants because of the nature of the intervention. However, the assessors will be blinded to group allocation.

**Fig. 1 Fig1:**
[figure not shown]
The PLE^2^NO flowchart

### Sample size

The sample size was calculated based on the primary outcome (self-reported pain). The analysis were done by the program GPower 3.1 [67], based on a priori analysis with ANCOVA, using one covariate and two groups with 80 % power at a 5 % significance. According to McKnight’s study [68], a combined strength training and a self-management program, we fixed the effect size on 0.35 and determined we needed a total sample size of 67. Considering a possible dropout of 20 %, we aimed to recruit 80 subjects and allocated 40 subjects per group.

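### Recruiting 80 with 20% dropout leaves 64 participants, three fewer than the 67 the plan says it needs

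*Protocol article*

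**What the plan says.** All the figures are in the Sample size section of the protocol article. The calculation is for self-reported pain, the primary outcome, and was run in GPower 3.1, "based on a priori analysis with ANCOVA, using one covariate and two groups with 80 % power at a 5 % significance". The effect size comes from an earlier study of strength training combined with self-management: "we fixed the effect size on 0.35 and determined we needed a total sample size of 67". The allowance for losses follows directly: "Considering a possible dropout of 20 %, we aimed to recruit 80 subjects and allocated 40 subjects per group". Allocation is 1:1 (Participants and procedures). No other section gives a different dropout rate, requirement or target.

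**The concern.** A dropout rate is ordinarily a share of those recruited. Read that way, the recruitment target must still leave 67 participants after 20% have gone, and 80 does not. The requirement, the dropout allowance and the target therefore cannot all hold.

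At stake is the claim of 80% power at the plan's own dropout rate. The target also has a practical role: Participants and procedures says recruitment sessions carry on until the planned sample is reached, so the printed 80 decides when recruitment stops. The power statement is also likely to be cited when the results are interpreted, above all if the difference in pain is not significant.

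**Working it through.** **Inputs, all from the Sample size section.** Two groups, one covariate, significance level 0.05, target power 80%, effect size 0.35, requirement 67, dropout 20%, target 80 (40 per group). The section does not name the effect-size metric. I read it as Cohen's f, the effect-size input for ANCOVA in GPower; step 1 supports this.

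**Step 1: reproduce the 67.** Power of the ANCOVA F test comes from the noncentral F distribution with df1 = 1, df2 = N − 2 − 1 = N − 3 and noncentrality λ = f² × N, where f² = 0.35² = 0.1225.

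| N analysed | λ = 0.1225 × N | Power |
|---|---|---|
| 64 | 7.84 | 78.7% |
| 66 | 8.085 | 79.95% |
| 67 | 8.2075 | 80.56% |
| 80 | 9.80 | 87.1% |
| 84 | 10.29 | 88.7% |

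The smallest N with at least 80% power is 67, exactly the plan's figure. Two other readings do not give it: a one-sided test would need 52, and taking 0.35 as Cohen's d would need 259. So f = 0.35 is the reading that fits, which for two equal groups is a baseline-adjusted standardised difference of d = 2f = 0.70.

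**Step 2: apply the plan's dropout to its target.** 80 × (1 − 0.20) = 64, or 32 per group. The shortfall is 67 − 64 = 3. This step uses only the printed figures and does not depend on the effect-size metric.

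**Step 3: find the target that 20% dropout requires.** 67 / (1 − 0.20) = 83.75, rounded up to 84 (42 per group). Check: 84 × 0.80 = 67.2. The plan is 84 − 80 = 4 recruits short.

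**Step 4: see where 80 may have come from.** 67 × 1.20 = 80.4, which rounds down to 80. This multiplies by 1.20 where a loss of 20% requires division by 0.80. Even by that route, rounding up would give 81. The article shows no formula, so this origin is an inference.

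**Step 5: size the consequence.**

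- Power at 64 analysed is 78.7%, which is 80 − 78.7 = 1.3 percentage points below target.
- With 64 analysed, the effect detectable at 80% power is f = 0.356 instead of 0.35.
- The loss that 80 recruits can absorb is 80 − 67 = 13, and 13 / 80 = 16.25%.

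**The case against.** The strongest objection is that the effect is negligible. The shortfall is 1.3 points of power, the detectable effect moves by 0.006, and the 0.35 is a rounded value taken from one earlier study, so its own uncertainty is far larger. The 20% is worded as a possibility, not a forecast: with no losses power is 87.1%, and it stays above 80% up to 13 losses. All of this is true. It limits the weight of the point but does not make the three figures agree.

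A second objection is that adding 20% to the requirement is a common shorthand, so that 80 is the intended number and only the word dropout is loose. That may explain the figure. On the ordinary meaning, a share of those recruited, it is still wrong.

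A third objection is that dropouts may still contribute, because the Data analysis section assumes data missing at random and plans linear mixed models. That section, however, uses the mixed models to examine whether effects persist over time in the self-management and exercise group. The comparison between groups is an ANCOVA of change from baseline to post-intervention, and a participant without a post-intervention value adds nothing to it unless values are imputed. Such handling may be set out in an analysis plan not seen here. The Sample size section itself inflates for dropout, so it treats dropouts as lost to the analysis.

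**Conclusion.** The error is real and confined to the dropout step. At the stated 20% dropout, 80 recruits yield 64 for analysis against a stated need of 67. The target consistent with the plan's own inputs is 84.

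The mismatch of 64 against 67 rests on nothing beyond the printed figures and the usual meaning of dropout. The power figures also assume that 0.35 is Cohen's f, which is well supported because it reproduces 67 exactly, and that dropouts are not analysed. On those assumptions the loss is about 1.3 points of power. That does not threaten the trial's validity, but a sizing statement that the design does not deliver should be corrected.

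**What to change.** Change the dropout sentence in the Sample size section. The least costly version keeps the target of 80 (40 per group) and says that it retains 80% power with up to about 16% dropout (13 participants), and that power at 20% dropout (64 analysed) is 79%. This changes wording only; the price is a slightly less favourable stated tolerance.

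If the sponsor prefers to keep the 20% tolerance at 80% power, the target should read 84 (42 per group), at the cost of four more recruits.

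As an optional clarification, the same sentence could name 0.35 as Cohen's f, equivalent to d = 0.70 on the baseline-adjusted scale, so that it is not mistaken for d. The correction does not depend on this.

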### Participants and procedures

The recruitment and selection processes will be performed using the following eligibility criteria: (1) an age of 60 years old or older, (2) bilateral or unilateral KOA diagnosed according to the clinical and radiological criteria of the American College of Rheumatology (ACR) [69], and (3) participants who are independently mobile and literate. The exclusion criteria will be the following: (1) involvement in another intervention program (exercise, education or physical therapy), (2) the prior use of supplements (chondroitin and/or glucosamine sulfate) for at least three months, and (3) other pathologies (e.g., cardiovascular, respiratory, and musculoskeletal pathologies and cancer) that prevent the practice of physical exercise, (4) a mental/psychological state that hinders understanding the program, (5) surgery for knee replacement or a plan to undergo surgery to place a prosthesis within the next eight months, (6) an allergy to shellfish or another component of the supplements, and (7) administration (injections) of corticosteroids or hyaluronic acid in the last 6 months.

To avoid convenience sampling, the participants will be recruited from the Lisbon area, and different marketing strategies will be used to advertise and publicize the PLE^2^NO program. Social networks, newspapers, magazines, contacts with senior universities, health centers, churches and community centers, and the site of the Portuguese League Against Rheumatic Disease will be the main channels used for PLE^2^NO announcements.

All individuals interested in participating will be invited to an awareness session in which the details of the program will be explained, and the patients will complete an eligibility questionnaire, which is necessary to acquire more detailed information, including whether they have any allergies to components in the supplements. As many sessions as necessary will be performed until the expected sample size is attained. Anyone who is interested and fulfills the eligibility criteria will receive a request for an x-ray examination. The exam requests will be referred to a rheumatologist who will make the final diagnosis according to the ACR clinical and radiological criteria. This is a more specific diagnosis (86 %) than a simple clinical diagnosis (69 %) [70]. If the subject is found to be positive for KOA, he or she will be invited to a second interview during which consent will be obtained.

The randomization process will be performed on the baseline assessment day by the research team leader. The randomization sequence will be a 1:1 allocation to the two treatment arms.

### Interventions

The active treatment group will engage in self-management and exercise (SMEG), and the control group will engage in patient education (EG) only. The SMEG patients will receive a combination program including self-management and exercise that will be delivered on the same days twice per week. Each session will last 90 min. The first 30 min will be allocated for self-management, and the remaining 60 min will be used for exercise. The program will be offered in a group format that encourages interaction and socialization, which can help to counteract feelings of depression and isolation. To avoid any conflict of interest and because we believe that it will help support the participants’ adherence, maintenance and pain control, all participants will receive a supplement that consists of a combination of two main substances: 1500 mg of glucosamine sulfate and 1200 mg of chondroitin sulfate, in addition to two secondary substances: 100 mg of *Harpagophytum* extract and 10 mg of hyaluronic acid. The recommendation is to use two packets per day. The participants themselves will have to complete daily sheets that request information regarding pain levels that are assessed on a visual numeric pain scale [71] and a bi-daily supplementation diary. All participants will be covered by personal accident insurance.

### Self-Management and Exercise Group (SMEG)

#### Self-management component

The self-management component is based on a program that was developed at Stanford University, the Chronic Disease Self-Management Program (CDSMP) [32], which aims to develop self-efficacy and emphasizes skills mastery. These are accomplished through the weekly performance of specific behaviors and the receipt of feedback (action plan and problem solving). The contents of the program will include the following: self-management principles, managing symptoms, exercise and physical activity, communication skills, healthy eating, and managing medicines. The program will be administered by a certified Master Trainer and Leader of the CDSMP at Stanford University.

#### Exercise component

The exercise component is based on the Fit and Strong Program [72], Exercise for People with Arthritis (FEPA) [35] and the Taking Control with Exercise (Arthritis Foundation) program. This exercise program contains health-related (muscular resistance/strength, and flexibility) and skill-related (balance) physical fitness components. Additionally, the program will include socialization games that help to decrease symptoms related to pain, stress, depression, and fatigue. In addition to improvements in physical fitness, the development of self-efficacy in exercise is another goal.

The exercise session type includes a warm up for the first 5 min, followed by 15 to 20 min of recreation activity and balance exercise, 30 to 40 min of the strengthening exercises, and 10 to 15 min of stretching and relaxation exercises at the end.

Specific strength exercises will be performed to recruit specific muscle groups in the lower limbs (quadriceps, hamstrings, hip adductors/abductors, gluteus, and gastrocnemius) and the upper limbs (pectoralis, trapezius, dorsal, deltoids, biceps and triceps). The strength exercises will use a combination of elastic bands (upper limbs) and cuff weights (lower limbs) or calisthenics, as previously used in other studies [73, 74] and replicated in the Fit and Strong program [72]. The resistance will be progressively increased throughout the program by adding weights in increments of 0.250 Kg to the cuff weights. The progressions in the numbers of repetitions and series are illustrated in Table 1.

**Table 1 Tab1:** Training volume

Week 1-3	Week 4-6	Week 7-9	Week 10-12
No additional load	Load 1	Load 2	Load 3
Week 1: 1 × 12 rep	Week 4: 1 × 12 rep	Week 7: 1 × 12 rep	Week 10: 1 × 12 rep
Week 2: 2 × 8 rep	Week 5: 2 × 8 rep	Week 8: 2 × 8 rep	Week 11: 2 × 8 rep
Week 3: 2 × 12 rep	Week 6: 2 × 12 rep	Week 9: 2 × 12 rep	Week 12: ×12 rep

The prescribed intensity and management of exercise resistance will be primarily guided by answers related to self-reported pain, which will be assessed using a Visual Numeric Pain Scale [71] before, during and after each session. At the beginning of each session, all participants will be required to present their pain diaries. If the pain level is above five points on the day before the last session, the load will not be increased, but if pain is below five points, they patients will receive increased loads. The intensity interval desired for strengthening exercises will be maintained at 4-6 (somewhat easy – somewhat hard) according the Omni-Perceived Exertion Scale for Resistance Exercise (OMINI-RES) [75].

This component will be overseen by a professional with a master’s degree in Science of Physiotherapy and another individual who is an Exercise and Health master’s student. Both will be from the Faculty of Human Kinetics.

To develop exercise self-efficacy and promote the maintenance of the exercise program before the end of the class, a chart with the main exercises for each physical fitness component (i.e., muscular resistance/strength, flexibility, and balance) will be given to the participants during the last two weeks of the intervention program. The participants will be encouraged to perform the exercises by themselves by following the chart during the last two weeks with supervision from the same professionals that conducted the exercise program. It is expected that they will develop the capacity to perform the exercises by themselves in their homes without supervision by the end of the intervention.

